### Protocol modifications

The procedure for implementing substantial protocol modifications requires submitting all changes to the Ethics Review Committee of the Second Affiliated Hospital of Xinxiang Medical University for approval. Upon receiving approval, the research team will formally notify all relevant stakeholders in writing. Subsequently, the approved amendments will be promptly recorded on the Chinese Clinical Trial Registry platform.

### Dissemination policy

Prior to enrolling any participants, the research team will register and disclose the trial details on the Chinese Clinical Trial Registry. Furthermore, there is a commitment to publicly release the complete study outcomes. The dissemination of results will be achieved through presentations at international conferences and submissions for peer-reviewed publication in scientific journals.

### Confidentiality

Regarding confidentiality, all study personnel have received training and certification in human subjects’ research protections through the Second Affiliated Hospital of Xinxiang Medical University Training Program. The Principal Investigator provides ongoing training and oversight to the evaluation coordinator to maintain the confidentiality and privacy of all participants and their data.

### Data sharing

Raw data will be generated at the Second Affiliated Hospital of Xinxiang Medical University. Derived data supporting the findings of this study will be will be accessible upon request from the corresponding author.

## Discussion

To the best of our knowledge, this may represent the first randomized, double-blind, controlled clinical trial investigating the potential of combining MRI-guided HD-tDCS with AE to enhance cognitive function for CIAS at the individual level. Most non-pharmacological interventions focus exclusively on either HD-tDCS or AE. HD-tDCS has been demonstrated to enhance executive function and working memory by modulating neuronal excitability in the mPFC (60). Meanwhile, AE influences brain plasticity, metabolism, structure, and connectivity by promoting neurogenesis and structural changes, thereby improving cognitive function (28, 61). Here in, we aim to integrate these two non-pharmacological approaches to examine their synergistic effect on cognitive enhancement for CIAS. This synergistic intervention strategy may break through the limitations of single intervention and provide aa multi-dimensional view of cognitive improvement. This could eventually provide individualized precision treatment strategies to increase treatment effectiveness.

This prospective, randomized, double-blind, controlled study will utilize MRI-guided HD-tDCS targeting mPFC to improve cognitive function for CIAS. Considering the significant impact of inter-individual neuroanatomical differences on HD-tDCS outcomes, MRI was employed to precisely identify and localize the target region for each participant. This customized approach ensured accurate electrode positioning, thereby enhancing stimulation precision and efficacy. Previous HD-tDCS research has demonstrated significant improvements in cognitive symptoms, particularly in executive functions (13, 62, 63). Given its role in advanced cognitive regulation, decision-making, working memory, and emotion control (64), the mPFC is a crucial brain region involved in the pathophysiology of schizophrenia. Its functional abnormalities are associated with CIAS, including impairments in working memory and attention control (65). Autopsy studies have demonstrated a significant reduction in the density of dendritic spines within the mPFC neurons of patients with schizophrenia (21). Studies utilizing animal models have revealed that abnormal dopaminergic regulation of the mPFC contributes to cognitive impairment (19). Investigations employing conventional HD-tDCS have indicated that stimulation of the mPFC can enhance language fluency and working memory in patients (66). Consequently, the mPFC may serve as a potential target for CIAS.

AE as an adjunctive intervention for chronic schizophrenia, may improve cognitive functions across five domains: information processing speed, working memory, problem-solving skills, verbal learning and memory, and visual learning and memory, consistent with previous research findings (33). Learning and memory functions are associated with the mPFC and hippocampus (67). Individuals with schizophrenia exhibit irregularities in neural growth and neurotransmitter release in mPFC (40), as well as alterations in hippocampal volume and morphology (68, 69). AE has been shown to improve mitochondrial structure and function in the mPFC, increase the release of neurotrophic factors such as BDNF (38), enhances aerobic metabolism (70), and mitigates hypoxia and inflammation (43, 71). AE interventions contribute to increased hippocampal volume in individuals with schizophrenia (72, 73), as well as elevated levels of oxygenated hemoglobin in the mPFC, which are closely linked to improved executive function (28). Animal studies using schizophrenia models further confirmed that exercise enhances hippocampal volume and cognitive abilities (73). Collectively, these findings imply that AE may improve cognition by modulating brain function and neurotransmitter release in the mPFC, which are critical for cognitive processes.

This study explores the integration of MRI-guided HD-tDCS with AE to enhance cognitive function in individuals with CIAS. This combined approach holds potential for mitigating adverse drug reactions, such as extrapyramidal symptoms and endocrine disorders, thereby improving patients’ overall quality of life. In other words, this approach provides a scalable non-pharmacological intervention, particularly advantageous for patients who experience limited drug efficacy or intolerable side effects. AE could simultaneously enhance cerebral blood flow and elevate neurotrophic levels, and achieve a synergistic effect when combined with electrical stimulation. This application could amplify therapeutic outcomes through a synergistic process. HD-tDCS can be safely administered in domestic settings, eliminating the need for frequent hospital visits and thereby reducing time and transportation costs. The flexibility of AE allows patients to select exercise methods tailored to their individual conditions, potentially improving adherence to interventions among individuals with CIAS and facilitating long-term treatment possibilities. In comparison to more complex neuroregulation techniques such as transcranial magnetic stimulation, this integrated strategy may overcome the limitations of single interventions. In the long term, it demonstrates high cost-effectiveness and is particularly suitable for implementation in community settings and low-income regions.

In this study, we will employ multi-dimensional measures to investigate the biological mechanisms of HD-tDCS combined with AE in individuals with CIAS. With the progress in individualized precision medicine, researchers are seeking biomarkers to guide therapy or access patient outcomes in schizophrenia. MRI data will be utilized to determine the optimal electrode placement, accounting for individual anatomical variations, and to evaluate alterations in brain structure and function. The HD-tDCS will target the mPFC to modulate neuronal excitability, with MRI employed to assess potential morphological enhancements in this region following the intervention, thereby providing structural-level support for cognitive enhancement. fNIRS will be used as a direct measure of neural activity to evaluate both local and network effects (74–76). Due to its high temporal resolution, robust resistance to motion artifacts, and cost-effectiveness (77), fNIRS is well-suited for the dynamic assessment of changes in brain function during interventions. Previous research has demonstrated a significant reduction in oxygenated hemoglobin signals within the mPFC during VFT in individuals with schizophrenia, which was negatively associated with cognitive performance (78). This study will utilize fNIRS to quantitatively evaluate the activation patterns of the mPFC, thereby providing objective insights into the neural mechanisms underlying a combined intervention. Previous research has demonstrated that AE can increase BDNF levels (38). Furthermore, P300, and EEG will be employed as objective measures to deliver a more comprehensive and systematic analysis of the neural mechanisms involved in the combined intervention. We hypothesize that the combined strategy may induce significant changes in mPFC activity and BDNF levels. We also hypothesize that these changes will correlate with improvements in cognitive function. If so, the study will provide objective evidence supporting the efficacy of HD-tDCS combined with AE, underscoring its potential as an individualized therapeutic strategy for addressing CIAS at the biological level.

This study presents some limitations. Firstly, the lack of a “sham” exercise or “sham” HD-tDCS compromises the complete blinding of participants, which may enhance the “expectancy effect” within the combined group. Although this study primarily investigates the synergistic feasibility of the two active interventions, future research should incorporate Sham-tDCS and an Active Control condition (such as stretching or low-intensity tasks) to balance “attention time” and “treatment expectation” across all participant groups. Secondly, cognitive tasks during treatment were not included in this study. Future research should incorporate cognitive tasks (such as N-back) concurrently with the intervention measures to enhance the magnitude and specificity of cognitive improvement. Thirdly, the sample size is relatively small, potentially compromising statistical power. Fourthly, the study lacks an analysis of various parameters of AE, Consequently, future research should focus on enlarging the sample size, and investigating optimal AE parameters. Fifthly, this study is the single center design, which may have a center effect and a selection bias. Further larger, prospective, multicenter studies are worthwhile.

This randomized, double-blind, controlled clinical design incorporated a multi-dimensional assessment will provide biological insights for the synergistic effect of HD-tDCS and AE on cognitive improvement. The integration of MRI-guided HD-tDCS targeting the mPFC with AE constitutes a promising avenue for cognitive rehabilitation in schizophrenia. This approach holds significant translational and clinical potential in precision psychiatry. Implementing these individualized therapeutic strategies may yield substantial clinical and economic benefits in the management of CIAS.

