## Methods

### Study design

This randomized, double-blind, controlled clinical trial evaluates the efficacy of combining HD-tDCS with AE to improve cognitive function in individuals with CIAS. Eligible participants will be randomly assigned to one of four groups in equal proportions (1:1:1:1): MRI-guided HD-tDCS +AE (Group 1), MRI-guided HD-tDCS alone (Group 2), AE alone (Group 3), and a control group (Group 4). Assessments will be conducted at baseline (T0), at 2 weeks (T1), at 4 weeks (T2), and at 6 months post-intervention (T3). The specific intervention measures for each group are delineated as follows: the MRI-guided HD-tDCS + AE group first undertakes a 15-minute warm-up exercise. Subsequently, HD-tDCS and AE treatments are administered concurrently for a duration of 30 minutes. The HD-tDCS group receives 30 minutes of electrical stimulation per session. The AE group’s intervention comprises a 15-minute warm-up followed by a 30-minute formal AE stage, amounting to a total of 45 minutes. The control group does not receive HD-tDCS or AE but instead is provided with routine psychiatric care, including regular psychiatric follow-ups, medication management, and general health guidance, but no experimental interventions. Each intervention for the aforementioned groups is conducted once daily, five days a week, over a period of four weeks, culminating in a total of 20 sessions. The study design is illustrated in **Figure 1**.

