A 48-channel functional near-infrared spectroscopy (fNIRS) device (NirScan model from Danyang Huichuang Medical Equipment Co. Ltd in China) will be employed in this study. The fNIRS data will be collected during the administration of The Chinese version of the Verbal Fluency Test (VFT) serves to evaluate verbal fluency, working memory, verbal recall, attention, and retrieval capabilities. The VFT task is structured into three distinct phases: a 30-second pre-task baseline period, a 60-second task period, and a 70-second post-task period. The baseline phase is characterized by the absence of VFT task performance. During the 30-second pre-task baseline phase, participants are instructed to count repeatedly from one to five until the commencement of the task period. In the subsequent 60-second VFT task period, participants are required to generate as many phrases as possible using simple words such as “white,” “north,” and “big.” Following the completion of the phrase generation task, participants are instructed to resume counting from one to five repeatedly throughout the 70-second post-task period. Fifteen light source probes and sixteen light detector probes will be positioned on the bilateral frontotemporal cortex, with a distance of 3 cm maintained between each light source and detector probe. In accordance with the 10/20 electrode placement system, the central probe will be positioned at FPz, while the lower boundary of the probe array will extend from Fp1 to Fp2. Hemodynamic changes will be assessed through measurements of oxyhemoglobin, deoxyhemoglobin, and total hemoglobin. Resting-state and task-state fNIRS data acquisitions will be performed for all participants in this study. The raw fNIRS data will be preprocessed utilizing the MATLAB Home 3 toolkit. Five statistical metrics—mean, variance, skewness, kurtosis, and peak value—will be calculated for changes in oxy-Hb signals, based on the spatial average across all 48 channels. This methodology will generate a total of 240 independent features for each subject.

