
To explore the underlying mechanisms, the study adopted a multimodal assessment framework. MRI and fNIRS were utilized to investigate changes in brain activity, structure, and functional connectivity. EEG and P300 were employed to capture the neurophysiological dynamics of electrical brain activity. EM served as an objective behavioral-physiological marker of cognitive processing. Additionally, plasma BDNF levels were measured to evaluate the molecular correlates of neurotrophic support and plasticity. This integrated approach aims to elucidate the therapeutic effects of MRI-guided HD-tDCS combined with AE for CIAS and to uncover the neurobiological mechanisms underlying these effects.The procedure for the site visit is outlined in **Table 2**.

**Table 2 T2:** Time schedule of screening, interventions and assessments.

Item	Recruitment	Assessment time point			
		T0	T1	T2	T3
Prescreening for eligibility, consenting, and clinical interview							
Recruitment					
Eligibility screening	✓				
Informed consent	✓				
Allocation	✓				
Primary outcome assessment					
MCCB		✓	✓	✓	✓
Second outcome assessment					
RBANS		✓	✓	✓	✓
BPRS		✓	✓	✓	✓
SQLS		✓	✓	✓	✓
SDSS		✓	✓	✓	✓
PEPT		✓	✓	✓	✓
VEPT		✓	✓	✓	✓
WCST		✓	✓	✓	✓
Biological assessment					
fNIRS		✓	✓	✓	✓
EEG		✓	✓	✓	✓
EM		✓	✓	✓	✓
P300		✓	✓	✓	✓
MRI		✓	✓	✓	✓
Plasma BDNF		✓	✓	✓	✓
Safety					
ARS			✓	✓	✓

A checkmark (✓) indicates the time point at which each assessment is carried out. ARS, Adverse Reaction Scale; BPRS, Brief Psychiatric Rating Scale; EEG, Electroencephalography; EM, Eye Movements; fNIRS, Functional Near-Infrared Spectroscopy; MCCB, MATRICS Consensus Cognitive Battery; MRI, Magnetic Resonance Imaging; PANSS, Positive and Negative Syndrome Scale; PEPT, Facial Emotion Perception Test; P300, P300 Event-Related Potential; RBANS, Repeatable Battery for the Assessment of Neuropsychological Status; SDSS, Social Dysfunction Screening Scale; SQLS, Schizophrenia Quality of Life Scale; VEPT, Voice Emotion Perception Test; WCST, Wisconsin Card Sorting Test.

T0: baseline, T1: after 2 weeks, T2: after 4 weeks, T3: after 6 months.

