### Sample size calculation

We performed the necessary calculations using G*Power software (version 3.1.9.7). Under the following command, test family: F tests; Statistical test: ANOVA: Repeated measures, within-between interaction (58).The research parameters were defined as follows: a Type I error rate of 0.05, a statistical power of 80%, and an effect size of 0.25. Utilizing a repeated measures ANOVA model and considering a potential participant dropout rate of 20%, we determined that the required sample size is 48 patients, with 12 patients assigned to each group. In preliminary studies where prior sample size data are unavailable, a group size of 12 subjects is deemed appropriate. We will justify the rationale for selecting a sample size of 12 per group from three perspectives: feasibility, improved precision in estimating means and variances, and adherence to regulatory requirements (59). This sample size is expected to provide adequate statistical power to address the study objectives.

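### The Discussion would take biomarker change plus its correlation with cognitive change as evidence of efficacy, but neither condition names a comparison between randomised arms

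*Protocol article*

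**What the plan says.** The Discussion of the protocol article sets out a chain of two conditions and a conclusion.

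- Condition 1: "We hypothesize that the combined strategy may induce significant changes in mPFC activity and BDNF levels".
- Condition 2: "We also hypothesize that these changes will correlate with improvements in cognitive function".
- Conclusion: "If so, the study will provide objective evidence supporting the efficacy of HD-tDCS combined with AE".

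The design has comparators. Under Study design, "Eligible participants will be randomly assigned to one of four groups in equal proportions (1:1:1:1"), with arms for the combination, HD-tDCS alone, AE alone and routine care. Statistical methods plans between-group and within-group models over time for the primary and secondary outcomes, with a likelihood ratio test of treatment and its interaction with time. The biomarkers are not among the secondary outcomes in Table 1 or the Outcomes section. Outcomes presents them as mechanistic measures, although it also says of the whole framework: "This integrated approach aims to elucidate the therapeutic effects of MRI-guided HD-tDCS combined with AE for CIAS".

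**The concern.** A correlation between two change scores tests whether marker and cognition move together. It does not test whether treatment moved either of them. A change within the combined arm does not test that either, because it contains whatever would have happened without treatment.

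The trial offers ordinary routes to both conditions without a treatment effect. The MCCB and the fNIRS recording, made during a verbal fluency task, are each scheduled four times, so practice can move both. The limitations paragraph concedes that there is no sham and that expectancy may be raised in the combined group. The Discussion also cites earlier evidence that AE raises BDNF, so the BDNF condition could be met by exercise alone and still be credited to the combination. Only a contrast with the AE arm would separate these.

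At stake is a claim of objective support for efficacy that the randomised comparison does not back. That situation is realistic: there are 12 patients per arm, and the article itself concedes that power may be limited.

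**Working it through.** **The plan's own figures.** The article gives no error rate for this inference, so there is none to reproduce. The sample size ("we determined that the required sample size is 48 patients, with 12 patients assigned to each group") was calculated for a repeated-measures interaction and does not bear on this point. It only supplies the group sizes below.

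**Inputs from the article.** n = 12 per arm, N = 48 in total, significance at 0.05 (taken as two-sided), two markers (mPFC activity and BDNF).

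**Assumptions, not in the article.** One summary measure per marker. Correlation r between each marker's change and cognitive change, arising without treatment: 0.3 or 0.5. The two markers are related only through cognition. A marker trend common to all four arms of 0, 0.5, 0.8 or 1.0 SD of change. No treatment effect in any arm.

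**Tests.** Condition 1 is a one-sample t test of change in the combined arm, t = mean change / (SD/√12), on 11 df, significant for both markers. Condition 2 is a Pearson test, t = r√(n − 2)/√(1 − r²), significant for both markers. Whether condition 2 uses the combined arm (n = 12) or all patients (n = 48) is not stated, so both are shown. There were 40,000 simulated trials per row.

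**Each part for one marker.** The change test is significant in 5%, 35%, 71% and 88% of trials at trends of 0, 0.5, 0.8 and 1.0 SD. The correlation test is significant in 16% (r = 0.3) and 40% (r = 0.5) in the combined arm, and in 55% and 96% pooled.

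**Both conditions, both markers, no treatment effect:**

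| r | Trend (SD) | Both changes significant | Both correlations, arm / pooled | All conditions met, arm | All conditions met, pooled |
|---|---|---|---|---|---|
| 0.3 or 0.5 | 0 | under 1% | 3–18% / 31–92% | under 1% | under 1% |
| 0.3 | 0.5 | 14% | 3% / 31% | 0.2% | 4% |
| 0.3 | 0.8 | 52% | 3% / 31% | 1% | 16% |
| 0.3 | 1.0 | 78% | 3% / 31% | 2% | 24% |
| 0.5 | 0.5 | 16% | 18% / 92% | 2% | 14% |
| 0.5 | 0.8 | 54% | 18% / 93% | 8% | 49% |
| 0.5 | 1.0 | 79% | 18% / 92% | 13% | 73% |

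The last columns are close to the product of the parts. In the last row, 0.79 × 0.92 = 0.73 pooled, and 0.79 × 0.18 = 0.14 in the arm (simulated 13%).

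**Dropout.** At the planned 20% loss, 12 × 0.8 = 9.6 per arm remain. With 10 per arm, the last row falls to 7% (arm) and 56% (pooled).

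**With a comparator.** Replacing the within-arm change by a combined-versus-control contrast on both markers brings every row to about 0.1% or less (arm) and 0.4% or less (pooled), whatever the common trend.

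**The case against.** The strongest defence is that this is an interpretive sentence in the Discussion, not an analysis rule. Efficacy is the primary objective and MCCB change the primary outcome. Statistical methods tests that outcome between arms by intention to treat. Nothing lets a biomarker result override it, and the sentence speaks of supporting evidence, not proof. The verb "induce" in condition 1 is causal and may have been meant relative to control. All biomarkers are scheduled at every visit without restriction by arm, so the contrasts could be made.

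Most of this stands, and it limits the point to the biomarker conclusion. It does not supply the missing comparator. The inference is stated, and it is invalid as stated, so it is more than a detail left to an analysis plan.

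Three stronger readings are tempting, and the article does not support them.

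- A reader might infer that a correlation alone would count, and quote the 55% and 96% above as false-claim rates. They are not: the text also requires significant change, and in both markers.
- A reader might infer that the inference would usually misfire. The high rates need pooling, r = 0.5 in both markers and a trend of 0.8 to 1 SD together. The article supports none of these values, and without a trend the rate is under 1%.
- A reader might add the 240 fNIRS features and a Bonferroni correction limited to time points. The conditions name mPFC activity and BDNF only. Feature choice and multiplicity for exploratory markers commonly belong to an analysis plan, which is not shown.

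**Conclusion.** The point holds as a fault of inference. Meeting the two conditions would not show that the combination works, or that it does more than either component, because neither condition uses the randomisation. That conclusion needs no simulation.

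The size is conditional on the assumed correlation and trend, and on which patients enter the correlation. The article fixes none of these, so the ranges in the table show sensitivity and do not predict this trial. A reader might infer that the trial's efficacy result is compromised. It is not: the between-arm MCCB analysis is untouched. The correction is worth making because a null MCCB result would otherwise leave a written licence to claim efficacy from the biomarkers.

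**What to change.** Reword the conclusion in the Discussion, and carry three statements into the analysis plan.

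1. Evidence of efficacy comes only from the randomised between-arm comparison of MCCB change.
2. Change in mPFC activity and in BDNF is compared between arms, the combined group against each of the other three, before it is attributed to the combination.
3. The association between biomarker change and cognitive change is estimated in a model that includes arm, and is reported as exploratory mechanistic evidence.

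The cost is some wording and a little extra analysis of measurements already scheduled in all four groups; no new data are required. The price is a weaker mechanistic claim. With 12 patients per arm, between-arm biomarker contrasts may well be inconclusive, and the report would have to say so.
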